#### Participant retention

Once a participant is enrolled or randomised, the local site will make every reasonable effort to follow the patient for the entire study period. It is estimated that loss to follow-up/withdrawal after randomisation will be no more than 10%. Study site staff are responsible for developing and implementing local standard operating procedures to achieve this.

#### Statistical methods

The formal statistical analysis plan will be finalised before database lock and before any statistical analysis.

A consort diagram will be presented. All continuous variables will be described using the mean, SD, median, minimum and maximum. Categorical variables will be described using frequencies and proportions.

The statistical assumptions underpinning each method will be checked. The use of transformations or non-parametric methods will be considered to satisfy statistical assumptions.

#### Primary outcome analysis

The primary analysis will be based on an intention to treat sample as well as a per protocol sample.

Our primary end point is the difference in proportion of men with clinically significant cancer detected between the two groups.

Absolute differences in proportion of clinically significant cancer detected between arms will be calculated with 95% CIs.

If the lower bound of the 97.5% CI for the difference in detection rates of MPMRI+/- targeted biopsy compared with TRUS biopsy is greater than −5% then MPMRI+/-- targeted biopsy will be deemed non-inferior.

In the event that the lower bound is greater than zero, superiority can be claimed.

Baseline characteristics will be compared between the two groups. Any imbalance found between the groups will be accounted for in a multivariable logistic regression analysis. This model will include clinically significant cancer as the dependant variable, group as the independent variable and any characteristics with baseline imbalance as a covariate. Potential confounders identified a priori will also be considered in the model described here. Here, the effect of centre will also be explored using a mixed logistic regression model with clinically significant cancer as the dependant variable, group as the independent variable and centre as a random effect.

The effect of missing data will be explored and dealt with in an appropriate manner.

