#### Sample size

Rates of clinically significant cancer detection from targeted-alone biopsy in a population with no prior biopsy have been shown to be 50%.^11^ Assuming 20% of men avoid biopsy in the MRI arm of PRECISION, this would correspond to a 50% detection rate in 80% of the participants in this arm =40% overall detection rate of clinically significant cancer in the MRI arm.

Rates of clinically significant cancer detection from one of the largest studies of TRUS biopsy in men without prior biopsy are shown to be 27%.^12^

For the non-inferiority hypothesis, using 90% power and 2.5% one-sided α, using an estimate for detection rate of clinically significant cancer for targeted biopsy of 40% and an estimate of detection rate for TRUS biopsy of 30% and using a margin of clinical unimportance of 5%, 211 men per arm will be required. The choice of 5% as the margin of non-inferiority represents a difference that would be considered clinically unimportant in the detection rates.

Thus the total men required in the study is 422.

Accounting for 10% withdrawal/loss to follow-up, 470 men will need to be recruited.

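### The primary decision rule rests on a 97.5% CI whose sidedness is not stated, so two thresholds can be read from it, only one of which matches the design alpha and power

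*Protocol article*

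**What the plan says.** The Sample size section of the Protocol article sets the design error rate: "For the non-inferiority hypothesis, using 90% power and 2.5% one-sided α". With detection rates of 40% (MPMRI arm) and 30% (TRUS arm), it continues: "using a margin of clinical unimportance of 5%, 211 men per arm will be required".

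The Primary outcome analysis section then makes three statements about one estimate, the difference in detection rates.

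- Reporting: "Absolute differences in proportion of clinically significant cancer detected between arms will be calculated with 95% CIs".
- Non-inferiority: the rule begins "If the lower bound of the 97.5% CI for the difference in detection rates" and requires that bound to lie above −5%.
- Superiority: it may be claimed if the lower bound, which can only be the bound just mentioned, lies above zero.

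Neither the 95% nor the 97.5% interval is labelled one-sided or two-sided. The section on secondary outcome analyses also uses 95% CIs without a label.

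**The concern.** Two confidence levels are given for one difference in adjacent statements, and the level that decides the trial is the one whose meaning is unclear. An effect estimate with an unlabelled 95% CI is conventionally two-sided. A reader who carries that convention into the rule would compute a two-sided 97.5% interval and so test at one-sided 1.25%, half the alpha used for the sample size. A reader who starts from the one-sided 2.5% alpha would take 97.5% as its complement and compute a one-sided bound.

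At stake is whether one dataset gives one verdict. If the observed difference falls between the two thresholds, competent analysts could disagree on non-inferiority or superiority, and the disagreement would surface after the results are known.

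**Working it through.** **Inputs** (Sample size section): detection rates 0.40 (MPMRI) and 0.30 (TRUS), margin 0.05, one-sided alpha 0.025, power 90% (z = 1.2816), 211 per arm.

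**Step 1. Reproduce the plan's figure.** With unpooled variance, n per arm = (z_α + z_β)² × [p₁(1−p₁) + p₂(1−p₂)] / (difference + margin)².

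- Variance term: 0.40×0.60 + 0.30×0.70 = 0.45.
- Distance from the margin: 0.10 + 0.05 = 0.15, squared 0.0225.
- n = (1.960 + 1.2816)² × 0.45 / 0.0225 = 210.1, rounded up to 211 per arm and 422 in total.

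This matches the plan exactly, so the trial was sized for a bound with z = 1.960.

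**Step 2. Critical value under each reading.**

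- One-sided 97.5% bound: z = 1.960. This is also the lower limit of a two-sided 95% CI.
- Two-sided 97.5% CI: 1.25% in each tail, z = 2.241.

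**Step 3. Power and thresholds at 211 per arm.** SE = √(0.45/211) = 0.0462.

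- Non-inferiority power = Φ(0.15/SE − z).
- Superiority power = Φ(0.10/SE − z).
- Observed difference needed for non-inferiority = −0.05 + z×SE.
- Observed difference needed for superiority = z×SE.

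| Quantity | One-sided 97.5% (= two-sided 95% lower limit) | Two-sided 97.5% |
|---|---|---|
| One-sided alpha | 2.5% | 1.25% |
| Non-inferiority power | 90.1% | 84.3% |
| Observed difference needed, non-inferiority | +4.1 points | +5.4 points |
| Observed difference needed, superiority | +9.1 points | +10.4 points |
| Superiority power (none is claimed) | 58.1% | 47.0% |

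A simulation of 400,000 trials with a Wald interval agrees: non-inferiority power 90.1% and 84.1%, superiority power 58.1% and 47.4%.

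**Step 4. How often the readings disagree at the planned rates.** Non-inferiority: 90.1% − 84.3%, about 6% of trials. Superiority: 58.1% − 47.0%, about 11%. The planning difference of 10 points lies between the two superiority thresholds, so a trial observing exactly 40% and 30% would claim superiority on one reading and not on the other.

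**Step 5. Sample size if the two-sided reading were meant.** n = (2.241 + 1.2816)² × 0.45 / 0.0225 = 248.2, so 249 per arm and 498 in total. Allowing for 10% loss, 498/0.9 gives 554 recruited, against the stated 470. This is a further sign that the design did not have that reading in mind.

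**The case against.** The strongest reply is that the plan is coherent once its two sections are read together. The alpha is stated as one-sided 2.5%, and its complement is a one-sided 97.5% bound. The rule uses only the lower bound and runs in one direction. No multiplicity adjustment is stated that would explain a 1.25% level. A two-sided 95% interval for reporting and a one-sided 97.5% bound for the decision share the same lower limit, so the two statements need not conflict. A formal analysis plan is to be finalised before database lock and could settle the label.

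Most of this stands. The one-sided reading is the more natural one and probably the intended one. A reader might infer from the unlabelled 97.5% that the rule contradicts the design alpha, or that the trial does not have its stated 90% power. The documents do not support either inference: both depend on taking the interval as two-sided, which the article never says. Nor does the ambiguity threaten a false claim of non-inferiority, because the two-sided reading is stricter and cannot raise type I error above the planned level.

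What the reply does not remove is that the article itself states the decision threshold, and states it so that a literal reader who treats all its intervals alike gets a different test from the one the trial was sized for. That is more than a detail deferred to an analysis plan.

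**Conclusion.** The point holds as one of unstated sidedness in the primary decision rule. It is not a demonstrated error in alpha, power or sample size. On the one-sided reading everything agrees and the power is 90.1%. On the two-sided reading the one-sided level is 1.25%, non-inferiority power is about 84.3%, and each threshold moves up by about 1.3 points (0.281 × 0.0462, the change in z times the SE).

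These figures assume the plan's rates of 40% and 30%, the 5-point margin, 211 evaluable men per arm and a normal approximation with unpooled variance. If all 470 men were evaluable (235 per arm), power on the two-sided reading would be 88.2%, still short of 90%. The superiority figures describe where verdicts could diverge and are not a shortfall, since the plan claims power for non-inferiority only.

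The correction deserves to be made because the sentence decides the trial and a single meaning can be fixed in advance.

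**What to change.** Replace the two decision sentences in the Primary outcome analysis section with wording such as: *Non-inferiority will be concluded if the lower limit of the two-sided 95% CI (equivalently the one-sided 97.5% lower confidence bound, one-sided alpha 2.5%) for the detection rate in the MPMRI arm minus that in the TRUS arm is above −5 percentage points. Superiority will be concluded if that same limit is above 0.* Report that one interval throughout, and carry the same sentence into the statistical analysis plan.

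The cost is one sentence in each document before database lock. It needs no extra patients or data, and the 211 per arm, the 470 recruited and the 90% power statement are unchanged.

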#### Sequence generation

Randomisation schedules are be prepared by a member of the UCL Surgical and Interventional Trials Unit using a bespoke SAS programme, with equal allocation between treatment arms using random permuted blocks of varying size, stratified by centre.

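### Randomisation is stratified by centre, but no centre adjustment is stated for the risk difference that decides the trial; a centre-stratified interval would be a small, nearly free gain in efficiency and alignment

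*Protocol article*

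**What the plan says.** Under Sequence generation, the allocation schedule is built "using random permuted blocks of varying size, stratified by centre".

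Under Primary outcome analysis, the effect measure is an absolute difference: "Absolute differences in proportion of clinically significant cancer detected between arms will be calculated with 95% CIs". The decision rule uses the same quantity. It begins "If the lower bound of the 97.5% CI for the difference in detection rates" and requires that bound to exceed −5%. A second rule follows: "In the event that the lower bound is greater than zero, superiority can be claimed". None of these sentences mentions centre.

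Centre comes in later in the same section, after the covariate-adjusted logistic model: "Here, the effect of centre will also be explored using a mixed logistic regression model". Its form is given as logistic, with "group as the independent variable and centre as a random effect". No conversion of its result to a risk difference is described.

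Under Statistical methods, a formal SAP is promised before database lock. It is not available here.

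**The concern.** Blocking within centre balances the arms inside each centre, so differences between centres largely drop out of the treatment contrast. A standard error computed from the two overall proportions still counts that between-centre variation. If centres differ, it is larger than the true sampling error of the difference, and the interval compared with −5 points and zero is wider than it needs to be.

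Some variation between centres is plausible from the protocol itself. It expects eleven countries, allows 1.5 or 3.0 Tesla scanners, visual or software registration, and a transrectal or transperineal route by local expertise.

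The second issue is scale. The one analysis that takes account of centre reports a conditional odds ratio, while the margin is an absolute difference. If the two analyses seem to disagree, the reader has no direct way to place the centre-aware result against the margin.

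At stake are a little precision and a clean match between design, margin and analysis.

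**Working it through.** **Inputs from the protocol (Sample size, Recruitment).** Detection rates 40% (MRI) and 30% (TRUS); margin 5 points; "using 90% power and 2.5% one-sided α"; 211 per arm; at least 11 centres. I use z = 1.96 for the lower bound, in line with the one-sided 2.5% of the sample size.

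**Input not in the protocol.** The between-centre SD of detection rates. Assumed 5, 10 and 15 percentage points.

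**Step 1. Reproduce the plan's figure.** n = (0.30×0.70 + 0.40×0.60) × (1.96 + 1.2816)² / 0.15² = 210.15, so 211 per arm and 422 in total. 422/0.90 = 468.9, close to the stated 470. The variance is the simple two-proportion one, with no centre term.

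**Step 2. Unadjusted standard error.** √(0.45/211) = 0.0462, so 1.96 × 0.0462 = 0.09055.

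**Step 3. Share of outcome variance due to centre.** At the mean rate of 35%: share = SD² / (0.35 × 0.65). The true SE under centre-blocked allocation is 0.0462 × √(1 − share), and the unadjusted interval is too wide by the factor 1/√(1 − share). Its one-sided error is Φ(−1.96 × factor).

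**Step 4. Non-inferiority power.** The distance from the planned effect to the margin is 0.10 + 0.05 = 0.15.
- Unadjusted: Φ((0.15 − 0.09055)/true SE). Blocking shrinks the sampling error of the unadjusted estimate too, so its power does not stay at the 90.1% that applies with no centre variation.
- Stratified: Φ(0.15/true SE − 1.96).

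| Assumed SD | Share | True SE | Excess width | One-sided error, unadjusted | Power, unadjusted | Power, stratified | Difference |
|---|---|---|---|---|---|---|---|
| 5 points | 1.1% | 0.04595 | 0.6% | 2.44% | Φ(1.294) = 90.2% | Φ(1.304) = 90.4% | 0.2 |
| 10 points | 4.4% | 0.04517 | 2.3% | 2.25% | Φ(1.316) = 90.6% | Φ(1.361) = 91.3% | 0.7 |
| 15 points | 9.9% | 0.04386 | 5.3% | 1.95% | Φ(1.355) = 91.2% | Φ(1.460) = 92.8% | 1.6 |

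**Step 5. Check by another route.** A normal centre effect on the logit scale was used, with a common odds ratio and overall rates held at 30% and 40%. For a logit SD of 0, 0.3, 0.5, 0.7 and 1.0, the excess width is 0%, 1.0%, 2.7%, 5.0% and 9.4%. Power, unadjusted against stratified, is 90.1/90.1, 90.3/90.7, 90.7/91.5, 91.2/92.7 and 92.1/94.4%. An SD of 0.7 already implies TRUS-arm rates of about 9% to 61% across the central 95% of centres. Simulation at the margin (30% against 25%, 11 equal centres, 40,000 runs) gave one-sided error for the unadjusted interval of 2.50%, 2.38%, 2.33%, 2.22% and 1.87%.

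**Step 6. The superiority rule.** With the same SEs and a true difference of 0.10, at SD 10 points: unadjusted Φ((0.10 − 0.09055)/0.04517) = 58.3%; stratified Φ(0.10/0.04517 − 1.96) = 60.0%. The gain is somewhat larger here, about 1.7 points, but the trial is not sized for this claim.

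**Step 7. Scale of the centre model.** The odds ratio equivalent to −5 points depends on the control rate:
- 27%: (0.22/0.78)/(0.27/0.73) = 0.76
- 30%: (0.25/0.75)/(0.30/0.70) = 0.78
- 40%: (0.35/0.65)/(0.40/0.60) = 0.81

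No single odds ratio stands for the margin. The random-intercept odds ratio is also conditional on centre: for 40% against 30% it is 1.59 at logit SD 0.5 and 1.70 at 1.0, against a marginal 1.56.

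**The case against.** The best reply is that nothing planned is harmed. The sample size uses the unstratified variance, so an unadjusted analysis is what the trial was sized for, and its power stays at or above 90%. The error is in the safe direction for a non-inferiority trial. That stands in full.

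The article also names no estimator. An absolute difference with a 95% CI could be a stratified one, and the SAP may say so. That stands in part. The article does give centre a specific place, as an exploration in a separate model, and an SAP that follows this text would leave centre out of the decision interval.

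Three stronger readings are tempting and are not supported:
- That the interval simply is too wide. This needs centres to differ, and the protocol gives no spread. Sites, MRI protocols, radiologists and biopsy operators are approved in advance, which may limit it. With no variation the excess is zero. If centres are regarded as a random sample, treatment effects that vary by centre could offset it.
- That ignoring centre endangers the non-inferiority conclusion. The calculations show the opposite direction.
- That the centre model cannot address the margin at all. This is true only of its raw odds ratio. The same model can be standardised to a risk difference. Nor does the protocol offer the model as the margin test.

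Stratifying is not quite free of side effects either. With a simple within-centre variance, the simulated one-sided error of the stratified interval was about 2.5% to 2.7%, so the variance method matters when centres are small.

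**Conclusion.** The point holds as a modest improvement. The design stratifies by centre, no centre adjustment is stated for the decision interval, and the only centre-aware analysis is exploratory and, as written, on a different scale from the margin.

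Under an assumed between-centre SD of 5 to 15 points, an unadjusted interval is about 0.6% to 5% too wide, one-sided error is slightly under 2.5%, and about 0.2 to 1.6 points of non-inferiority power are forgone (0.7 at SD 10). These figures assume balance within centre and a treatment effect that does not vary materially between centres. Planned power is met and false non-inferiority is not increased. This is a matter of efficiency and alignment; a non-inferiority finding from the unadjusted interval would not be invalid on this ground.

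**What to change.** State in the SAP, before database lock, that the interval judged against −5 points and zero is a centre-adjusted risk difference. Either of two forms will do:
- a Mantel-Haenszel weighted risk difference across centres, with a variance suited to small strata (for example Sato or a Newcombe-type interval);
- a logistic model with centre, standardised to a marginal risk difference with its CI.

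Add a pre-stated rule for pooling very small centres, for example by country. Keep the unadjusted difference as a sensitivity analysis. If the mixed logistic model is retained, report its result on the risk-difference scale as well.

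The cost is a few sentences of SAP text and a few lines of code. The sample size need not change, and the pooling rule is the only new decision.

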#### Secondary outcome analyses

The effect sizes will be presented with 95% CIs.

For binary outcomes, absolute differences in proportion between arms will be calculated with 95% CIs. Any imbalance found between the groups will be accounted for in a multivariable logistic regression analysis.

For continuous outcomes, mean differences in outcomes between arms will be calculated with 95% CIs. Any imbalance found between the groups will be accounted for in a multivariable linear regression analysis. Where the outcomes are not normally distributed, a suitable transformation or non-parametric test will be considered.

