#### Patient-reported outcome measures

In both arms self-reported questionnaires to capture biopsy-specific side effects will be completed immediately postprocedure, and at 30 days. Health-related quality of life EQ-5D-5L questionnaires will also be completed at baseline, 24 hours post-MRI, 24 hours post biopsy and 30 days post intervention.

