#### Secondary outcomes

Please see table 2 for a full list of secondary outcomes.

**Table 2 T2:** Secondary outcomes in PRECISION

Outcome	Time frame for assessment
Proportion of men with clinically insignificant cancer (Gleason grade 3+3) detected	When histology results available, at an expected average of 30 days post intervention
Proportion of men in the MPMRI arm who avoid biopsy	When MRI results available, at an expected average of 30 days post-MRI
Proportion of men in whom the MPMRI score for suspicion of clinically significant cancer was 3, 4 or 5 but no clinically significant cancer was detected	When histology results available, at an expected average of 30 days post biopsy
Proportion of men who go on to definitive local treatment (eg, radical prostatectomy, radiotherapy, brachytherapy) or systemic treatment (eg, hormone therapy, chemotherapy)	After treatment decision, at an expected average of 30 days post biopsy
Cancer core length of the most involved biopsy core (maximum cancer core length, mm)	When histology results available, at an expected average of 30 days post intervention
Proportion of men with post biopsy adverse events	30 days post biopsy
Health-related quality of life	Baseline, 24 hours post intervention and 30 days post intervention
Proportion Gleason grade upgrading in men undergoing radical prostatectomy	An expected average of 90 days post biopsy
Cost per diagnosis of cancer	30 days post biopsy

MPMRI, multi-parametric MRI.

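### EQ-5D-5L has a scheduled baseline value, but the article adjusts for covariates only when an undefined imbalance is found, which gives up precision and lets the data choose the estimate

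*Protocol article*

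**What the plan says.** Under Patient-reported outcome measures, the protocol article states that "EQ-5D-5L questionnaires will also be completed at baseline, 24 hours post-MRI, 24 hours post biopsy and 30 days post intervention". Table 2 lists health-related quality of life as a secondary outcome with the time frame "Baseline, 24 hours post intervention and 30 days post intervention". Tables 1A, 1B and 1C all place the questionnaire at visit 1, before any trial procedure.

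Secondary outcome analyses fixes the method for every continuous outcome: "For continuous outcomes, mean differences in outcomes between arms will be calculated with 95% CIs". It then gives the only route by which a covariate can enter: "Any imbalance found between the groups will be accounted for in a multivariable linear regression analysis". Neither that section nor Primary outcome analysis says what counts as an imbalance.

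Primary outcome analysis does mention covariates chosen in advance: "Potential confounders identified a priori will also be considered in the model described here". That sentence refers to the logistic model for clinically significant cancer, not to quality of life. Statistical methods adds that "The formal statistical analysis plan will be finalised before database lock and before any statistical analysis".

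**The concern.** The value of a baseline covariate lies in how well it predicts the outcome. Whether the arms happen to differ on it is a separate matter, and in a randomised trial such a difference arises by chance. A rule that adjusts only after an imbalance is seen therefore selects on the wrong criterion and leaves the covariate out of most trials in which it would have helped.

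Because imbalance is undefined, the reported estimate may be adjusted or unadjusted according to a judgement made once the data are visible.

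At stake is the width of the confidence interval for one secondary outcome, and whether its estimator is fixed in advance. Among the continuous outcomes the point concerns EQ-5D-5L only: maximum cancer core length has no baseline value.

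**Working it through.** **Inputs from the article.** One-sided α 2.5%, power 90%, detection rates 40% (MRI) and 30% (TRUS), margin 5%, 211 per arm, 10% loss, 470 recruited (Sample size); 1:1 allocation (Randomisation and treatment allocation).

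**Inputs assumed.** The baseline-to-follow-up correlation ρ is not given, so 0.3, 0.5 and 0.7 are used. Results are in SD units because no SD is given. The 211 per arm is carried over as the number with EQ-5D-5L data; the variance ratios do not depend on it.

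**The plan's own figure.** n = (1.96 + 1.2816)² × (0.40×0.60 + 0.30×0.70) / (0.10 + 0.05)² = 10.507 × 0.45 / 0.0225 = 210.1, so 211 per arm. Then 422/0.9 = 468.9, so 469, or 470 for two equal arms. The stated size reproduces. It concerns the primary outcome; no size is stated for EQ-5D-5L.

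**Always adjusting against not adjusting.** For a linear model with baseline as covariate, the variance of the arm effect is (1 − ρ²) times that of the unadjusted follow-up mean difference. The unadjusted 95% half-width is 1.96 × √(2/211) = 0.191 SD.

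| ρ | variance factor 1 − ρ² | half-width (SD) | interval narrower by | equivalent unadjusted n per arm, 211/(1 − ρ²) |
|---|---|---|---|---|
| 0.3 | 0.91 | 0.182 | 4.6% | 232 |
| 0.5 | 0.75 | 0.165 | 13.4% | 281 |
| 0.7 | 0.51 | 0.136 | 28.6% | 414 |

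The last column only restates the variance factor. A difference that the unadjusted comparison detects with 80% power (two-sided 5%) is (1.96 + 0.8416) × √(2/211) = 0.273 SD; with adjustment its power is 84%, 90% or 98%.

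**The rule as written.** Since no trigger is defined, a baseline test at p<0.05 was assumed and simulated (20,000 trials per ρ, normal data, 211 per arm).

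| ρ | baseline used in | variance relative to unadjusted: trigger rule | always adjusted | type I error, trigger rule |
|---|---|---|---|---|
| 0.3 | 5.0% | 0.98 | 0.91 | 4.9% |
| 0.5 | 5.1% | 0.93 | 0.75 | 4.5% |
| 0.7 | 5.0% | 0.87 | 0.52 | 3.6% |

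Most of the available gain is lost. The simulation standard error of the type I error is √(0.05×0.95/20,000) = 0.15 percentage points, so 4.9% is indistinguishable from 5%. The other two values are below nominal, that is, conservative.

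**If change from baseline were meant.** With equal SDs at both times, the variance factor for a change score is 2 − 2ρ = 1.4, 1.0 or 0.6. Adjustment for baseline (0.91, 0.75, 0.51) is better at each value.

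**The case against.** The strongest reply is that the article condenses a fuller plan. Its sentence on continuous outcomes is generic, a formal statistical analysis plan is promised before database lock, and the model for one patient-reported outcome is normally settled there. That has force against any claim that baseline adjustment is missing. It does not meet the present point, because the article states a rule, and an analysis plan that followed it would carry the imbalance trigger forward.

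Four stronger readings are tempting, and the article does not support them:

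- **That raw follow-up means will be compared.** The article does not say raw or unadjusted. Table 2 lists baseline among the assessment times, which would also fit a change score or a longitudinal model. What the text fixes is a mean difference with covariates conditional on imbalance.
- **That the result would be biased.** Under randomisation the unadjusted difference is unbiased, and its interval already allows for chance baseline differences.
- **That the loss is large.** The article gives nothing on how strongly baseline EQ-5D-5L predicts follow-up. At ρ = 0.3 the interval narrows by under 5%.
- **That a main conclusion is at risk.** Quality of life is not among the key secondary objectives named under Objectives. Table 3 does list it under a key-outcomes label, but with all the other secondary outcomes. No margin, power or decision rule rests on it.

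It is also fair to say that the existing regression provision would catch a conspicuous baseline difference, and that the article already allows for transformations or non-parametric methods with non-normal data.

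**Conclusion.** The point holds as one of efficiency and prespecification for a single secondary outcome. Adjusting for EQ-5D-5L only after an undefined imbalance is inferior to adjusting always. The gain forgone is about 5% to 29% of confidence interval width for assumed correlations from 0.3 to 0.7, with 13% at 0.5. These figures rest on a linear relation between baseline and follow-up and on a correlation that the article does not supply; the simulated behaviour of the rule rests further on the assumed p<0.05 trigger. The lack of a definition for imbalance is a fact of the text and depends on no assumption.

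The 24-hour assessment needs separate care. It follows biopsy in the TRUS arm, both MRI and biopsy in MRI-arm men with a target, and MRI alone in MRI-arm men without one. It is therefore not the same event in all men, and the 30-day comparison is the natural place for the adjusted analysis.

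**What to change.** For EQ-5D-5L, replace the imbalance rule with a prespecified linear model of the 30-day score on arm and baseline EQ-5D-5L, fitted whatever the observed imbalance. Include centre, because Sequence generation makes it the stratification factor. Use the same baseline adjustment at 24 hours wherever the arms are compared at a matching post-intervention assessment, and state which assessment is meant. Specify robust or bootstrap confidence intervals if the index is skewed.

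The cost is wording in the statistical analysis plan. No visit, form or patient is added. If the plan already specifies this model, the sponsor need only confirm that it supersedes the rule in the article.
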